**Nodal tumour load**

As previously mentioned, the SLN is negative in 74% of clinically node negative patients in the general breast cancer population. This percentage is lower in breast cancer patients with small primary breast tumours and if treated with breast conserving therapy. Patients treated with breast conserving therapy are significantly more often diagnosed with pathologic node negative disease or with micrometastatic disease, compared to patients treated with mastectomy (p <0.0001) [50]. The addition of axillary ultrasound to the preoperative nodal staging will increase the percentage of SLN negative patients to 84% in cT1-2N0 breast cancer patients treated with breast conserving therapy [51].

**Micrometastases in the sentinel node**

In the above mentioned 84% SLN negative patients, micrometastatic disease is considered as node- positive. The presence of micrometastasis in the SLN however, has no significant impact on overall survival and it is therefore questionable whether these patients benefit from adjuvant systemic therapy [50, 52, 53]. Other analyses have shown that small occult lymph node metastases (mostly isolated tumour cells or micrometastases) in patients with sentinel nodes that were negative on initial examination, were not associated with worse survival [54, 55]. Routine immunohistochemical examination and serial sections of haematoxylin-eosin-negative SLN’s are therefore no longer standard procedure in many clinics worldwide. Exclusion of these techniques in the Netherlands as well, would increase the number of SLN negative patients even further. In the study of Weaver et al., 4.4% of occult metastases were micrometastases (11.1% isolated tumour cells; 0.4% macrometastases) [54]. About 20-

25% of node positive patients would therefore be counted as node negative when excluding routine immunohistochemical examination and serial sectioning, resulting in an increased percentage of SLN negative patients with 4% to 88%.

**Nodal tumour load in our proposed study population**

Combining the above described results leads to the following percentage of node negative patients and leads to the following nodal tumour load in (occult) node positive patients in our proposed study population:

[figure not shown]

[figure not shown]

[figure not shown]

**Conclusion**

In conclusion, the NSABP B-04 randomized controlled trial showed us that omitting primary axillary
treatment of occult positive lymph nodes in clinically node negative breast cancer patients does not affect survival, even after 25 years of follow-up and without the use of adjuvant systemic or radiation therapy. The performance of a delayed ALND in case axillary lymph nodes become clinically positive does not affect survival and prevents axillary overtreatment in the majority of patients. The ACOSOG Z0011 and the IBCSG 23-01 randomized controlled trials revealed that completion ALND can be safely omitted in clinically node negative breast cancer patients with metastatic sentinel nodes. Patients randomized for watchful waiting were likely to have residual nodal disease (13-27%) that was not surgically removed. Nevertheless, survival rates were not affected and regional recurrence rates low. Clinically node negative patients in these trials were selected by physical examination. Adding axillary ultrasound will improve the preoperative selection of node negative patients, as it selects patients with a more favourable tumour load and accurately excludes advanced nodal disease (≥4 metastatic nodes). Biology, adjuvant systemic therapy and standard tangential breast irradiation are all factors that most likely diminish the risk that possible metastases left in situ develop into clinically detectable lymph nodes. Patients treated with breast conserving therapy are more likely to have pathologic node negative or micrometastatic disease, compared to patients treated with mastectomy. The risk for occult (macro)metastases in our study population is low: about 88% will be node negative and about 95% of node positive patients will have no lymph node metastases beyond the SLN. Reflected by the low regional recurrence rate after a (false) negative SLN, only a small amount of patients (0.8%) with node positive disease is expected to develop clinically detectable nodal disease.

**The study**

Therefore, we propose a randomized controlled trial to prove that the sentinel lymph node procedure can be omitted in clinically node negative breast cancer patients treated with breast conserving therapy. This study will significantly decrease the number of breast cancer patients receiving overtreatment of the axilla, thereby diminishing the risk for complications, while maintaining excellent regional control and not affecting survival, with an expected decrease of the annual breast cancer care expenditures.

**4. OBJECTIVES**

**Primary objective**

The primary objective of this study is to investigate whether omitting the sentinel lymph node procedure is not inferior to the current axillary staging regimen in clinically node negative breast cancer patients undergoing breast conserving therapy, in terms of regional recurrence rate.

**Secondary objectives**

Secondary objectives of this study are to investigate whether omitting the sentinel lymph node procedure is not inferior to the current axillary staging regimen in clinically node negative breast cancer patients undergoing breast conserving therapy, in terms of distant-disease free survival, overall survival rate, the local recurrence rate and the occurrence of contralateral breast cancer.

Other secondary objectives are the influence of omitting the sentinel lymph node procedure on the number of delayed axillary lymph node dissections, the administration of adjuvant systemic therapy, the axillary morbidity rate, quality of life and cost-effectiveness.

All objectives are measured during a follow-up of 10 years, and analyzed after 1, 3^1^, 5 and 10 years of follow-up.

**Hypothesis**

The sentinel lymph node procedure can be safely omitted in clinically node negative breast cancer patients undergoing breast conserving therapy. This will lead to a decreased axillary morbidity rate, with non-inferior regional control, distant-disease free survival and overall survival.

**5. STUDY DESIGN**

***a. Description of the study design***

A prospective non-inferiority randomized controlled multicentre trial, randomizing women aged 18 years

or older with pathologically confirmed unilateral cT1-2N0* invasive breast cancer about to undergo breast conserving surgery followed by radiotherapy of the breast to:

Arm A - control arm: lumpectomy with sentinel lymph node procedure, followed by radiotherapy of the breast with or without completion axillary treatment according to the Dutch breast cancer guideline.

Arm B - study arm: lumpectomy without further axillary staging, followed by radiotherapy of the breast.

* cT1-2N0: primary tumour not larger than 5 cm and clinically node negative based on a negative axillary ultrasound (or negative cyto-/histology).

*Stratification for the randomization arm*

Patients will be stratified by: age (≤50, 50≤75, >75 years old), oestrogen receptor status (positive vs. negative), HER2neu status (amplified vs. not amplified), clinical tumour stage prior to any treatment (<3 cm vs. ≥3 cm), grading (grade I-II vs. III - according to Bloom-Richardson grading system), will be or is treated with primary systemic therapy (yes vs. no), participating centre.

***b. Schematic study design***

Study design 1: if primary treated with breast conserving therapy

[figure not shown]

Study design 2: if primary with systemic therapy:

[figure not shown]

***c. Timeline***

**Jul 2014 - Jan 2015** review of the study

**May2015 - Apr 2021** Inclusion of patients (1644; 36 months)

Start of 10 year follow-up

**Apr 2021 - Apr 2026** Completion of 5 year follow-up of every patient

**Apr 2026 - Apr 2031** Completion of 10 year follow-up of every patient

**6. STUDY POPULATION**

***a. Population***

The incidence of invasive breast cancer in female patients in the Netherlands was approximately

14.000 in 2011.

***b. Inclusion criteria***

In order to be eligible to participate in this study, a subject must meet all the following criteria:

1. Female
2. Aged 18 years or older
3. Pathologically confirmed invasive unilateral breast carcinoma
4. A clinical T1-2 tumour
5. Will be treated with lumpectomy and whole breast radiotherapy
6. Clinically node negative status: no signs of axillary lymph node metastases at physical examination and preoperative axillary ultrasound (or negative cyto-/histopathology)
7. Written informed consent

Furthermore, primary systemic therapy is allowed if the patient has a clinical T1-2N0 status (initial stage) that is amenable to lumpectomy pre-systemic therapy.

***c. Exclusion criteria***

A potential subject who meets any of the following criteria will be excluded from participating in this

study:

1. Clinically node positive pre-operative
2. Bilateral breast cancer
3. Evidence of metastatic disease
4. History of invasive breast cancer
5. Previous treatment of the ipsilateral axilla with surgery or radiotherapy, except surgery for

hidradenitis suppurativa or for other superficially located skin lesions, such as naevi

1. Pregnant or nursing
2. Other prior malignancies within the past 5 years, except successfully treated malignancies that occurred more than five years before randomization, and except successfully treated basal
   cell and squamous cell skin cancer, carcinoma in situ of the cervix or carcinoma in situ of the
   ipsilateral or contralateral breast
3. Unable or unwilling to give informed consent

***d. Sample size calculation***

Sample size calculation for a non-inferiority design including clinically node negative breast cancer

patients treated with breast conserving therapy, who will be randomized between SLN procedure versus no further axillary staging is as follows: Our hypothesis is that clinically node negative patients treated with breast conserving therapy who do not undergo the SLN procedure will have a non-inferior regional recurrence rate compared to patients in the control group and should therefore be treated as such.

Prior data indicate a 5-year regional recurrence free survival rate of 99% for the control patient group. The expected true regional recurrence free survival rate for the experimental patient group is 96% (taking into consideration the higher morbidity rate caused by axillary treatment in the control arm), and a difference of more than 5% in favour of the control patient group (the upper limit of a one-sided 95% confidence interval) is not accepted. The expected regional recurrence free survival rates and the non- inferiority limit of 5% (delta) result in a sample size of 747 per arm, to be able to reject the null hypothesis that the rate for experimental and control subjects is inferior by at least 5%, with a probability of 0.8.

|  | **p1** | **p2** | **Alpha  (type I error)** | **Power** | **Epsilon (p1-p2)** | **delta** | **Sample Size**  **(per arm)** |
| --- | --- | --- | --- | --- | --- | --- | --- |
| **Non-Inferiority** | 0,96 | 0,99 | 0,05 | 0,8 | -0,03 | -0,05 | 747 |

When taking into account a lost to follow-up rate of 10%, **1644** patients need to be randomized. In the Netherlands, every year **14.000** female patients are diagnosed with invasive breast cancer. About 80 % is operated on primarily (when excluding patients treated with systemic therapy only, or patients with primary metastatic disease and frail elderly).

| 14.000 * 80% = **11.200** patients  Of these patients, 80% is cN0.  11.200 * 80% = **8.960** patients  In the Netherlands 54% of the patients are treated with breast conserving therapy and 46% undergo  mastectomy.  8.960 * 54% = **4.838** patients  With the now known interest in participating of 43 hospitals in the Netherlands, 59% of the patients will visit a study hospital.  4.838 * 59% = **2.854** patients  We expect an accrual rate of 30%  2.854 * 30% = 856 patients yearly  This means that **3 years** will suffice to include **1644 patients (including 10% lost to follow-up)** |
| --- |
|  |
|  |
|  |

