***h. Withdrawal of individual subjects***

Patients can leave the study at any time for any reason if they wish to do so without any consequences,

and without having to specify the reason for withdrawal. The investigator can decide to withdraw a subject from the study for urgent medical reasons. Withdrawal of patients during the follow-up period will be counted to the 10% of lost to follow-up.

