***j. Final statistical analysis***

Primary and secondary endpoints will be analysed per protocol and in the intention to treat population

after 5 and 10 years of follow-up. Primarily, uncorrected chi-squared statistics will be used to evaluate the null hypothesis, as described in chapter 6, section d ‘Sample size calculation’ on page 19. The chi- square test will be based on the Kaplan-Meier estimator, in case of censored data. Additionally, cox proportional hazards models and Kaplan Meier estimates will be used to analyse the outcome of both groups and to assess the univariable and multivariable association between prognostic variables, treatment and events, using the stratification factors. All statistical tests are 1-sided and a P value of 0.05 or less is considered statistically significant.

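### Section 6.d reaches 1644 by multiplying 1494 by 1.10 instead of dividing by 0.90, so with 10% loss about 740 per arm, not 747, complete follow-up; the effect on power is minor

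*Protocol*

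**What the plan says.** Section 6.d sizes a non-inferiority comparison of two 5-year proportions. For the control arm, "Prior data indicate a 5-year regional recurrence free survival rate of 99% for the control patient group". For the study arm, "The expected true regional recurrence free survival rate for the experimental patient group is 96" percent. The margin is 5 percentage points, assessed by "the upper limit of a one-sided 95% confidence interval", and the power is 0.8. These inputs "result in a sample size of 747 per arm".

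The attrition step follows: "When taking into account a lost to follow-up rate of 10" percent, 1644 patients are to be randomised. The accrual calculation at the end of 6.d repeats 1644 and describes it as already containing the 10% who will be lost. The inflation formula is not written out.

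Three other sections bear on the point:

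- Section 7.h (withdrawal of individual subjects) gives withdrawals no allowance of their own: "Withdrawal of patients during the follow-up period will be counted to the 10% of lost to follow-up".
- Section 7.j (final statistical analysis) bases the primary chi-square test on the Kaplan-Meier estimator if there is censoring, and confirms the level: "All statistical tests are 1-sided and a P value of 0.05 or less is considered statistically significant".
- The timeline (5.c) and the stopping rule (8.d) both use 1644 as the enrolment target.

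**The concern.** A reader who takes 10% off the stated 1644 should get back to the stated 747 per arm, and does not. The inflation adds 10% of the number needed at the end, whereas a loss rate applies to the number randomised at the start. The two operations give different totals, and the one used gives the smaller.

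The number of patients to randomise is the headline figure of the sample size section and recurs elsewhere in the protocol. A non-inferiority trial should have a size that can be reproduced from its own inputs, and the final report will have to quote it. What is at stake is the correctness of a stated figure. The validity of the design is not in question.

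**Working it through.** **Inputs, all from section 6.d:** study-arm proportion 0.96; control-arm proportion 0.99; margin 0.05; one-sided alpha 0.05 (z = 1.645); power 0.80 (z = 0.842); loss to follow-up 10%.

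**Step 1. Reproduce 747 per arm.**

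- Distance between the expected difference and the margin: 0.05 - 0.03 = 0.02.
- Sum of binomial variances: 0.96 x 0.04 + 0.99 x 0.01 = 0.0384 + 0.0099 = 0.0483.
- n per arm = (1.645 + 0.842)^2 x 0.0483 / 0.02^2 = 746.5, rounded up to 747.

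The stated 747 is therefore correct for its inputs. Two arms give 1494. A one-sided 0.025 level would have given 948 per arm, so 0.05 is indeed the level used.

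**Step 2. Reproduce 1644.**

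- 1494 x 1.10 = 1643.4, rounded up to 1644.
- Per arm: 747 x 1.10 = 821.7, rounded up to 822; 2 x 822 = 1644.

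The match is exact, so this is how the figure was obtained.

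**Step 3. Apply the stated loss rate to those randomised.**

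- Needed: 1494 / 0.90 = 1660, or 830 per arm. That is 16 more than 1644 (16 / 1644 = 0.97%).
- Left from 1644 after 10% loss: 1644 x 0.90 = 1479.6, or 739.8 per arm, about 7 per arm short of 747.
- Largest loss at which 1644 still leaves 1494: 1 - 1494 / 1644 = 150 / 1644 = 9.1%.

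**Step 4. Power if lost patients contribute nothing.**

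Power = Phi(0.02 / sqrt(0.0483 / n) - 1.645).

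- n = 747: 80.0%.
- n = 739.8: 79.7%.

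This is the worst case: it treats every lost patient as leaving on the day of randomisation.

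**Step 5. Power under the planned Kaplan-Meier-based test.**

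The protocol does not say when losses occur, so the following rests on assumptions: constant event hazards matching 0.96 and 0.99 at 5 years, 10% of each arm lost by year 5, and 822 randomised per arm. The variance in each arm is the large-sample Greenwood form, S(5)^2 times the integral from 0 to 5 years of hazard / (822 x G(t) x S(t)), where S is event-free survival and G(t) the proportion not yet lost. Effective n is 0.0483 divided by the sum of the two variances.

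| Timing of the 10% loss | Effective n per arm | Power |
| --- | --- | --- |
| All at randomisation | 740 | 79.7% |
| Half at randomisation, half evenly over 5 years | 760 | 80.6% |
| All evenly over 5 years | 780 | 81.5% |

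Power falls below 80% only if more than about 8 of the 10 percentage points are lost at randomisation.

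**The case against.** The strongest reply is that the error has no practical consequence. The planned test does not discard patients who leave early. Section 7.j uses Kaplan-Meier estimates, and the withdrawals that 7.h counts towards the 10% happen during follow-up, so those patients have observed time before they leave. Even the worst case of 79.7% rounds to the stated power of 0.8. The timeline gives a planned total and the accrual rule in 8.d is a judgement of feasibility; neither would change materially between 1644 and 1660. All of this stands, and it fixes the size of the point as minor.

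It does not make the attrition sentence correct. The protocol sized the trial on fixed proportions, chose to inflate for loss, and used the wrong operation.

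One could also argue that the 10% was meant as a share of the 1494. The text does not favour that: it calls the figure a rate of loss to follow-up and describes the 1644 as containing those lost.

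In the other direction, a reader might infer that with 10% loss the trial necessarily drops below 80% power, so that its size, loss rate and power cannot all be true together. The documents do not support that. Under the test in 7.j, 1644 randomised, 10% lost and 80% power are compatible unless nearly all losses come at the very start. What cannot hold together is 1644 randomised, 10% lost, and 747 per arm with complete follow-up.

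**Conclusion.** The inflation step in 6.d is wrong. With the stated 10% loss, 1644 leaves about 740 per arm with complete follow-up instead of 747, and it covers a loss of 9.1%. The correct inflation is 1660, a difference of 16 patients. These figures follow directly from the protocol's numbers and need only the plain reading that 10% of those randomised are lost.

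The effect on power is slight: 0.3 percentage points in the worst case (79.7% against 80.0%), and none below 80% when at least half of the losses are spread over follow-up (80.6% to 81.5%). The second statement depends on the assumed constant hazards and timing of loss, which the protocol does not give. The 747 per arm is itself correct, and the design is not threatened.

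**What to change.** Correct the attrition sentence in 6.d in one of two ways, and align the repeat of 1644 in the accrual calculation with it:

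- state that 1644 allows for 9.1% loss while keeping 747 per arm with complete follow-up, and that 10% loss would require 1660; or
- state that 10% loss from 1644 leaves about 740 per arm with complete follow-up, with power of 79.7% in the worst case where all losses occur at randomisation. The words about the worst case are needed, because the planned analysis is not restricted to patients with complete follow-up.

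The target in the timeline and stopping rule can stay at 1644. No extra enrolment and no change of design or analysis is needed. The only cost is a slightly less favourable stated figure.

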**7. METHODS**

1. ***Study endpoints***

**Main study endpoint**

⮚ *Regional recurrence rate*

Regional recurrence is defined as tumour recurrence and as residual tumour that became clinically

apparent in ipsilateral axillary, infraclavicular and supraclavicular lymph nodes (pathologically proven).

**Secondary study endpoints**

⮚ *Regional recurrence free survival*

Regional recurrence free survival is defined as the time interval between the date of randomization and the date of first suspicion of regional recurrence or date of death, whichever comes first, measured in days. Patients who did not experience regional recurrence and are still alive are censored at the date of last follow-up.

⮚ *Delayed axillary treatment*

This is defined as the number of patients in in whom delayed axillary treatment (any kind) >6 months

after randomization was performed in case of regional recurrence, with the time interval between the date of randomization and the date of the delayed ALND, measured in days.

⮚ *Distant-disease free survival*

Distant-disease free survival is defined as the time interval between the date of randomization and the

date of first suspicion of distant recurrence or death, whichever comes first, measured in days. Patients in whom a distant recurrence was not observed and are still alive are censored at the date of last follow- up.

Included are: distant recurrence (distant metastasis), death from breast cancer and its treatment, death from second primary invasive (nonbreast) cancer death from unknown cause. N.B.: lymph node recurrence in cervical lymph nodes or in contralateral internal mammary lymph nodes or in the contralateral axilla is coded as distant metastasis.

Excluded are: ipsilateral breast tumour recurrence, regional invasive recurrence, contralateral breast cancer, and all in situ carcinomas, as these events are potentially nonlethal.

⮚ *Overall survival*

Overall survival is defined as the time interval between the date of randomization until death from any

cause. Patients who are still alive are censored at the date of last follow up.

Included are: death from breast cancer, death from nonbreast invasive cancer cause, death from unknown cause.

⮚ *Local recurrence rate*

Local recurrence is defined as any pathologically proven invasive in-breast recurrence in the ipsilateral

breast after breast surgery. The local recurrence free interval is defined as the time interval between the date of randomization and the date of first clinical suspicion of local recurrence, measured in days.

⮚ *Other-regional recurrence rate*

Other-regional recurrence is defined as pathologically proven recurrence in the region of the ipsilateral

internal mammary lymph node chain (lymph nodes in the intercostal spaces along the edge of the sternum in the endothoracic fascia). Other-regional recurrence free interval is defined as the time interval between the date of randomization and the date of first clinical suspicion of other regional recurrence, measured in days.

⮚ *Contralateral breast cancer rate*

The occurrence of (pathologically proven) contralateral invasive breast cancer will be registered. Contralateral breast cancer free interval is defined as the time interval between the date of randomization and the date of first clinical suspicion of contralateral breast cancer, measured in days.

⮚ *Diagnosis of recurrence outside the axillary region*

One or more of the following must be positive for the diagnosis of tumour recurrence to be accepted:
I. Histology or cytology

II. Autopsy examination

Diagnosis based on radiological findings can be considered if I or II is not possible/available (these
cases will be presented to the Data Safety Monitoring Board (DSMB) for an independent review).

⮚ *Percentage difference in the administration of (neo)adjuvant systemic therapy*

This is defined as the percentage difference in the administration of (neo)adjuvant systemic therapy

between both study arms.

- *Quality of Life*

Quality of Life will be assessed using validated questionnaires, as shown in chapter 7 ‘METHODS’, section e ‘Study procedures - axillary morbidity rate and quality of life’ on page 27.

⮚ *Axillary morbidity rate*

The axillary morbidity rate will be assessed using validated questionnaires, as shown in chapter 7

‘METHODS’, section e ‘Study procedures - axillary morbidity rate and quality of life’ on page 27.
⮚ *Cost-effectiveness*

The cost-effectiveness will be assessed by using patient questionnaires, as shown in chapter 7 ‘METHODS’, section f ‘Cost-effectiveness analysis’ on page 28 and electronic Case Report Forms (eCRF) as shown in chapter 10 ADMINISTRATIVE ASPECTS AND PUBLICATION on page 34.

1. ***Study procedure – diagnosis and randomization***

*Diagnosis*

The study population will be selected from the group of patients visiting the hospital with breast complaints or patients referred by the breast cancer screening program. Eligibility for the study should be verified in every patient with invasive breast cancer. According to the standard care and work-up of breast cancer patients, general patient information and medical history will be obtained, and all patients will undergo standard preoperative physical and radiological examination (which may include mammography, ultrasound of the breast and axillary region, MRI of the breast, cytological and/or histological biopsies) according to the Dutch breast cancer guideline. Screening for axillary lymph node metastases with physical examination and an axillary ultrasound is obligatory.

*Axillary ultrasound*

The axillary ultrasound is standard of care in the preoperative diagnostic work-up of breast cancer patients according to the Dutch breast cancer guideline. The performance of the axillary ultrasound is standardized in this study to ensure its quality. Therefore the radiologist should perform the axillary ultrasound according to the following method:

Preferably, the patient is positioned with the ipsilateral hand placed behind the head. The entire axilla is examined in a standardized fashion, starting at the low axilla (level I: inferior and lateral to the pectoralis minor muscle), and continuing upwards toward mid-axilla (level II: medial and lateral to the pectoralis minor muscle and interpectoral) and apical axilla (level III: superior and medial to the pectoralis minor muscle with apical lymph nodes).

The following criteria are used during ultrasound to identify positive lymph nodes: long to short axis ratio of <2 (i.e. round), diffuse or focal cortical thickening, effacement or replacement of the fatty hilum, and/or nonhilar blood flow (using Doppler ultrasound, if detectable). As described in the Dutch breast cancer guideline, cortical thickening of more than 2.3 mm is considered as the optimal cut-off point to perform fine-needle aspiration biopsy. Additionally, a subjective assessment of thickening can be made by the radiologist during real-time imaging, similar to the studies by Koelliker et al, Abe et al, and Neal et al [37, 56, 57]. Fine-needle aspiration biopsy or core biopsy is recommended when suspicious lymph nodes are identified. Preferably, a core biopsy of a suspicious lymph node is performed instead of fine-needle aspiration biopsy, because core biopsy is more sensitive, as described by Rautiainen et al. [35]. In case of two or more abnormal lymph nodes, the lymph node with the most suspicious findings is selected for tissue sampling.

*Randomization*

In case a patient meets the inclusion criteria and breast conserving therapy is the choice of treatment (according the considerations of the surgeon and the patients’ preference), the patient will be asked to participate in the study by the attending surgeon. We will start the inclusion of patients immediately after the approval of the METC and the Executive Board.

⮚ *Written informed consent in patients undergoing primary surgical treatment*

This section is applicable in cases undergoing primary surgical treatment. Before the surgical treatment,

patients are informed about the goal, the randomization procedure and the consequences of participating. Written informed consent must be obtained and randomization performed preoperatively (lumpectomy ± SLN procedure). Randomization is performed centrally.

⮚ *Written informed consent in patients undergoing primary systemic treatment*

This section is applicable in cases undergoing primary systemic treatment. Primary systemic therapy is

allowed if the patient has a clinical T1-2 tumour (initial stage) that is amenable to lumpectomy pre- systemic therapy.

In case the SLN procedure is standardly performed *prior* to the primary systemic therapy, written informed consent must be obtained and randomization performed prior to the SLN procedure and primary systemic treatment. Subsequently, the SLN procedure is or is not performed according to the randomization arm, followed by the primary systemic treatment. If patients are not treated with breast conserving therapy after completion of the primary systemic treatment (for any reason) and are treated with a mastectomy, the SLN procedure should be performed for patients randomized to arm B.

In case the SLN procedure is standardly performed *after* the primary systemic therapy, written informed consent must be obtained and randomization performed after completion of the primary systemic treatment when the final decision is made that the patient is treated with breast conserving therapy.
Randomization is performed centrally.

⮚ *Stratification*

Patients will be stratified by: age (≤50, 50≤75, >75 years old), oestrogen receptor status (positive vs.

negative vs. unknown), HER2neu status (amplified vs. not amplified vs. unknown), clinical tumour stage prior to any treatment (<3 cm vs. ≥3 cm), grading (grade I-II vs. III - according to Bloom-Richardson grading system vs. unknown), will be or is treated with primary systemic therapy (yes vs. no), participating centre.

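### The event lists for overall survival and distant-disease free survival omit deaths from known non-cancer causes, which the definitions of both endpoints count as events

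*Protocol*

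**What the plan says.** Both definitions are in Protocol section 7.a, under Secondary study endpoints.

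**Overall survival.** The definition is "Overall survival is defined as the time interval between the date of randomization until death from any" cause. The censoring rule is "Patients who are still alive are censored at the date of last follow up". The list of events follows: "Included are: death from breast cancer, death from nonbreast invasive cancer cause, death from unknown cause".

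**Distant-disease free survival.** The interval runs from randomization to the "date of first suspicion of distant recurrence or death, whichever comes first, measured in days". Censoring is again limited to living patients: "Patients in whom a distant recurrence was not observed and are still alive are censored at the date of last follow" up. The list is "Included are: distant recurrence (distant metastasis), death from breast cancer and its treatment, death from second primary invasive (nonbreast) cancer death from unknown cause". A separate exclusion list names ipsilateral breast recurrence, regional recurrence, contralateral breast cancer and in situ carcinomas, on the ground that they need not be fatal.

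The secondary objectives and the hypothesis (section 4) claim non-inferiority on both endpoints. Section 7.j analyses them after 5 and 10 years.

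**The concern.** Each endpoint carries two event rules that do not agree. The definition sentence takes in every death. The list stops at cancer deaths and deaths of unknown cause (for DDFS, also deaths from breast cancer treatment). A woman who dies of a known cardiac, cerebrovascular or infectious cause meets the definition but not the list, and she cannot be censored because she is not alive.

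An analyst could follow either rule. Coding from the list would make OS partly cause-specific under the name of overall survival, and would narrow DDFS in the same way. Both estimates would be too high. Event status would also depend on how the cause of death was attributed, in a trial whose arms differ by a visible surgical procedure and whose protocol describes no blinding.

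These deaths are to be expected. Section 6.b sets no upper age limit, section 5.a has a stratum above 75 years, and follow-up lasts 10 years. The protocol's own Markov model (section 7.f) has separate states for death from cancer and death from other causes.

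**Working it through.** **1. The rules side by side, applied to a death from a known non-cancer cause**

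| Element of section 7.a | OS | DDFS |
|---|---|---|
| Definition | Event: death from any cause | Event if no earlier distant recurrence: death, cause not qualified |
| Censoring rule | Not applicable: patient not alive | Not applicable: patient not alive |
| List of included events | Not named | Not named |
| List of excluded events | No such list | Not named (only events that need not be fatal) |

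For OS the list contradicts the definition outright. For DDFS the list is narrower than an unqualified word; the phrase *any cause* is not used there. Regional recurrence free survival, in the same section, counts death without any list of causes, so it does not have this conflict.

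**2. What the plan's own figure depends on**

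The protocol gives no event count, power or mortality for OS or DDFS. Its only computed design figure is the sample size in section 6.d, with expected rates of 0.99 and 0.96, margin 0.05, one-sided alpha 0.05 and power 0.80:

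n = (1.645 + 0.842)² × (0.99×0.01 + 0.96×0.04) / (0.05 − 0.03)² = 6.183 × 0.0483 / 0.0004 ≈ 747 per arm.

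Total: 2 × 747 × 1.1 = 1643.4, rounded up to 1644.

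Both figures reproduce, and neither uses the OS or DDFS lists.

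**3. Illustration for 5-year OS if the list were used for coding**

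Input from the protocol: N = 1644. Assumptions, because the protocol has no mortality figures: 5-year all-cause mortality m of 5-8%, and a share s of 20-50% of deaths from known non-cancer causes.

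- Deaths by year 5: 1644 × 0.05 = 82 to 1644 × 0.08 = 132.
- Deaths not on the list: 20% of 82 = 16 to 50% of 132 = 66.
- Overstatement if these deaths are simply not counted, m × s: 0.05 × 0.20 = 1.0 point to 0.08 × 0.50 = 4.0 points.
- Overstatement if they are censored instead, with constant hazards, (1−m)^(1−s) − (1−m): 0.95^0.8 − 0.95 = 0.9598 − 0.95 = 1.0 point, to 0.92^0.5 − 0.92 = 0.9592 − 0.92 = 3.9 points.

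The two ways of following the list give nearly the same answer.

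**4. Sensitivity to the assumptions**

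Taking instead a 5-year risk of known non-cancer death of 1-10% and of listed-cause death of 3-5%, with constant hazards and censoring, 16 to 162 deaths fall off the list and the gap in 5-year OS is about 1.0 to 9.7 points. At 3% for both risks it is 49 deaths and 0.970 − 0.941 = 2.9 points. The size therefore follows mainly from the assumed non-cancer mortality.

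No figure is given for DDFS. The direction is the same, but only deaths without an earlier distant recurrence matter there.

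**The case against.** The best defence is that the lists are the outlier. The OS definition, both censoring rules and the DDFS exclusion list all fit the reading that every death counts. The lists also look loosely drafted: the second OS item is awkwardly worded, and the DDFS list lacks a separator before its last item. On this view they illustrate the definition, and a competent analyst would follow the definition.

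Much of this stands. A reader might infer that non-cancer deaths have no place in the analysis at all. The document does not support that: it follows only if the lists are exhaustive and override the definitions, and the protocol says neither. A reader might also infer that both endpoints are defined by death from any cause; only OS is.

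The defence does not remove the conflict. The lists open as statements of what is included, with nothing to mark them as examples, and DDFS pairs its list with one of exclusions, which is the form of a coding rule. No other section says which rule governs. The statistical analysis plan, which was not available for this point, may settle the derivation, but the protocol text would still contradict itself.

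The second objection concerns size. The stated aim is a comparison between arms, and omitting non-cancer deaths would raise the OS level in both. That stands too: nothing here shows that such deaths, or their attribution, would differ by arm.

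**Conclusion.** The inconsistency is real and should be fixed on these two secondary endpoints. A death from a known non-cancer cause is an event under each definition, missing from each list, and cannot be censored. The conflict is direct for OS and weaker for DDFS, where it rests on an unqualified word.

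If the lists were used for coding, absolute OS and DDFS would be overstated. For 5-year OS the illustration is about 1-4 percentage points (16 to 66 of 82 to 132 deaths), on assumed mortality of 5-8% with 20-50% of deaths from known non-cancer causes. Other assumptions give other figures, and the overstatement does not arise if the definitions are followed.

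A reader might take the 1-4 points as bias in the non-inferiority comparison, or treat the point as a threat to the trial's main conclusion. Neither is supported. The figure describes the survival level, the effect on the arm difference is not quantified, and the primary endpoint, the margin and the 1644 patients do not depend on these lists.

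**What to change.** - **OS:** delete the list, or add an item for death from any other cause so that the list matches the definition.
- **DDFS:** state that death from any cause is an event. If a cause-specific version is wanted, name it as a separate endpoint and treat other deaths as competing events.
- Carry the same rule into the derivation of both endpoints in the statistical analysis plan.

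The cost is one sentence per endpoint and the matching derivation rule. No new data are needed and the sample size does not change. The change should be in place before OS and DDFS are derived.
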